## Abstract

**Introduction:**

Aboriginal and Torres Strait Islander peoples are the First Peoples of Australia. Up to 45% of dementia in these populations is due to potentially modifiable risk factors. The Dementia Prevention and Risk Management Program for Aboriginal Australians (DAMPAA) is an Aboriginal Health Practitioner led programme that aims to reduce cognitive decline and functional impairment in older Aboriginal people.

**Methods:**

Design: DAMPAA is a multisite, randomised controlled trial aiming to deliver and evaluate a culturally appropriate risk factor management programme. Population: Community-dwelling Aboriginal people aged 45–90 years. Intervention: Participants will be randomly assigned to either usual care (control) or to a group programme comprising exercise and health education yarning sessions and pharmacist-delivered medication reviews delivered over a 12-month period. Primary outcome: Cognitive function (Kimberley Indigenous Cognitive Assessment (KICA)-Cog score), daily function (KICA-Activities of Daily Living (ADL) score) and quality of life (Good Spirit, Good Life and EQ-5D-5L scores). Secondary outcomes*:* Process evaluation interviews, cardiovascular risk factors, falls and death. Process evaluation will be conducted with qualitative methods. Quantitative outcomes will be analysed with generalised linear mixed models.

**Ethics and dissemination:**

The study was approved by the Western Australian Aboriginal Health Ethics Committee and the University of Western Australia Human Research Ethics Committee. Study results will be published in peer-reviewed journals and presented at scientific meetings. We will also develop and disseminate a comprehensive DAMPAA toolkit for health services. The study’s findings will guide future prevention strategies and outline a comprehensive process evaluation that may be useful in other Aboriginal health research to contextualise findings.

Strengths and limitations of this studyTheory of change framework for co-design and process evaluation in partnership with Aboriginal Community Controlled Health Organisations.Aboriginal research methodologies including co-design workshops with Aboriginal Elders and community-controlled organisations, Aboriginal health practitioner-led programme, yarning education methods and Elders Governance Group.Randomised controlled trial design limits the flexibility required in Aboriginal health research.Lack of culturally specific neuropsychological test norms.Potential for experimental contamination due to the extended family structure of Aboriginal people.

## Introduction

### Background and rationale

 Aboriginal and Torres Strait Islander peoples (hereafter respectfully referred to as Aboriginal people^1^) are the First Peoples of Australia and the spiritual and cultural custodians of the land. Aboriginal Elders play a vital role in preserving traditional knowledge, language and culture.^2^ Their cognitive health is vital to enable them to preserve and teach culture, language and law to younger generations. As one Wunambal man said, ‘My grandfather, he still got all that memory in his head, and now he’s sharing that with us young fellas so that we can carry his way, the way he taught us, so that it can always be there for our kids, and their kids’.^3^

Dementia is a broad term for a group of conditions that affect cognitive functioning. Approximately 50 million people worldwide live with dementia, and this is expected to triple by 2050.^4^ Previously, identification of dementia in Aboriginal people was hampered due to the lack of a valid dementia screen. The Kimberley Indigenous Cognitive Assessment (KICA-Cog) was developed and validated in 2003 with Aboriginal people in the Kimberley region of Western Australia.^3 5^ This led to further research revealing that Aboriginal people experience dementia at a rate three to five times higher than the non-Aboriginal population—one of the highest in the world.^6^,^9^ The KICA has since been adapted and validated in other regions of Australia^8 10^ and adapted and validated for Torres Strait Islander peoples^9^ and for First Nations peoples internationally.^11 12^

While there is currently no cure for dementia, international studies have identified that up to 40% of dementia risk factors are potentially modifiable.^4^ A recent analysis identified that up to 45% of the dementia burden for Aboriginal and Torres Strait Islander peoples may be due to potentially modifiable risk factors.^13^ Potentially modifiable risk factors attributed to the high incidence of dementia in Aboriginal people include physical inactivity, high blood pressure, diabetes, head injuries, current smoking, obesity, stroke, epilepsy, polypharmacy, poor mobility and falls.^7 14 15^ In 2018–2019, 31% of Aboriginal and Torres Strait Islander adults had high blood pressure and 13% had diabetes or hyperglycaemia, while 71% of those aged ≥15 years were overweight or obese and 37% were daily smokers. Only 12% of adults living in non-remote areas met physical activity guidelines.^16^ There is a need for culturally safe health programmes targeting these modifiable risk factors.

Physical inactivity is a major risk factor for disease burden in Aboriginal people,^17^ while physical activity that starts in mid to late life can still significantly reduce the risk of cognitive decline.^18^ Regular physical activity has numerous benefits on cognition due to increased cerebral blood flow,^19^ neurogenesis and angiogenesis, synaptic plasticity, reduced inflammation and improved brain resilience.^20 21^ Physical activity interventions have demonstrated a decrease in cognitive decline^22^ and have preventive effects on cardiovascular disease, hypertension, diabetes, hypercholesterolaemia and obesity.^23^ Additionally, physical activity reduces falls risk,^24^ improves mobility^23^ and enhances quality of life.^25^ Australian health guidelines recommend 150 min of physical activity per week, including cardiovascular, resistance, mobility and balance components for older adults.^26^

Guidelines for physical activity programmes have been developed for people with mild cognitive impairment and other risk factors for dementia.^27^ Health programmes run by Aboriginal Community-Controlled Organisations (ACCOs) have been effective in improving specific health measures such as blood pressure, body mass index (BMI) and quality of life.^28 29^ Additionally, group and community activities centred on social interaction are preferred formats of physical activity for Aboriginal people,^30^ and when paired with culturally appropriate and relevant health education can lead to positive outcomes.^28 29^ Health messages delivered by Aboriginal people have a more profound impact on health behaviour^31^ and should underpin health education within Aboriginal communities. Yarning is a culturally respectful approach that Aboriginal people use to interact, convey knowledge and exchange narratives, either in a casual or formal setting, with one or multiple individuals.^32^ It is a method that can be used in Aboriginal health research and in the clinical environment to facilitate health education within Aboriginal communities.^33^ Social contact is a protective factor for dementia,^4^ with Aboriginal people emphasising the importance of strong social connections for a better quality of life in older age.^34 35^

Aboriginal health research occurs in complex contexts that present a unique number of organisational and community challenges.^36^ Staff shortages and absences, as well as high workforce turnover, particularly outside urban settings, are common challenges.^37^ Challenges for researchers include managing a project across distant locations, low recruitment numbers and providing an appropriate level of support to Aboriginal research staff to successfully carry out project objectives.^37^ Participant challenges to involvement in research include family commitments, attending funerals, caring for grandchildren, transport and other medical appointments which make it more difficult to prioritise commitments to a programme.^38^ In addition, dementia risk factor awareness in the Aboriginal community is low.^39^ Participant enablers for adherence to physical activity programmes include location and attending an Aboriginal centre with other Aboriginal people, transport assistance, enjoyment in programme activities and feeling healthy.^29 40 41^ A clear programme structure, access to varied exercise equipment and learning about health are also factors that enable increased adherence.^42^

A multi-domain, culturally safe and responsive programme specifically targeting modifiable risk factors to reduce cognitive decline in older Aboriginal people is required. Key principles for successful research with Aboriginal people include leadership and ownership by Aboriginal researchers, local development, commitment, control, supporting workers’ professional development, Aboriginal community capacity building and facilitating enablers to increase community participation.^29 37 42 43^

This paper describes the protocol for the Dementia Prevention and Risk Management Program for Aboriginal Australians (DAMPAA), co-designed to address the modifiable risk factors for dementia in Aboriginal people. The first participant was enrolled in October 2020 and the last enrolment was October 2023. Data collection will conclude in late 2024.

### Aims of the study

The overall aim of the DAMPAA project is to co-develop, deliver and evaluate a targeted culturally appropriate Aboriginal Health Practitioner (AHP) coordinated risk factor management programme to reduce cognitive decline and functional impairment in Aboriginal Australians aged 45 years and over at risk of dementia. This will be achieved by (1) co-designing a dementia risk reduction programme with and for Aboriginal people, and (2) conducting a randomised controlled trial comparing DAMPAA with usual care.

### Trial design

The DAMPAA trial is a multisite, randomised controlled trial, with randomisation at the individual level. In partnership with Elders and ACCOs in Western Australia (WA), we co-designed the AHP-led health programme for Aboriginal people aged ≥45 years using a Theory of Change (ToC) approach, as previously described.^38^

Process evaluation of the DAMPAA programme will occur through the ToC framework, using a qualitative approach.^38^ The COVID-19 outbreak in 2020 and subsequent restrictions led to the suspension of the pilot programme and study from March 2020 to September 2021. After the recommencement of the study, various WA government health restrictions limited research activities until March 2022 when all restrictions were removed. This paper describes the protocol of the DAMPAA programme post COVID-19 suspension. Figure 1 outlines the steps involved for participants joining the programme.

**Figure 1 F1:**
[figure not shown]
Dementia Prevention and Risk Management Program for Aboriginal Australians study participant journey.

## Methods

### Programme sites

Perth is the capital city of WA. Three programme sites were established across WA, with two in the Perth metropolitan area and one in the regional town of Geraldton with project partners.

### Participants

Inclusion criteria include: (1) Aboriginal person; (2) aged between 45 and 90 years; (3) community-dwelling; and (4) normal cognition (KICA-Cog score 38–39) or cognitive impairment without dementia (KICA-Cog score 31–37 without functional decline due to dementia). Exclusion criteria include: (1) dementia diagnosis; (2) presence of medical condition that restricts walking without assistance; (3) unstable or life-threatening medical condition; and (4) medical condition that contraindicates moderate physical activity, including morbid obesity (BMI≥40 kg/m^2^).

### Patient and public involvement

DAMPAA was co-designed with Elders and ACCOs. This process included elder yarning groups, workshops at three Aboriginal community controlled health services and a pilot programme run in Geraldton and Perth, WA.

### Terminology

The terms DAMPAA programme (intervention) and usual care (control) will be used in this paper based on the recommendation of our Aboriginal Elders Governance Group, who stated that ‘intervention’ and ‘control’ are not culturally safe terms in the Aboriginal community. This culturally safe terminology has also been followed in our study protocols and training manuals.

### DAMPAA group and programme

Participants randomised to the DAMPAA programme will complete the 12-month programme and assessments described later in this paper. The programme consists of two periods: the action period (1–6 months) and maintenance period (7–12 months). During the action period, participants will attend two group walking and yarning sessions per week at an ACCO and complete a third exercise-only session at home. Each session will be up to 90 min in duration. Participants will therefore be expected to engage in up to 270 min of DAMPAA programme activity per week. Sessions will be led by a trained exercise professional and AHP and will include a warm-up, walk, strength and balance exercises, stretching and cool down. The first 8 weeks of the programme will gradually acclimatise participants to exercise, with incremental increases in intensity each week. Session intensity will be monitored using the 1–10 rate of perceived exertion (RPE) measure and heart rate measures using Polar M200 heart rate watches. Participants will be set a target heart rate range each session that is individually calculated based on age and heart rate reserve. Each participant will complete a personalised goal-setting activity within the first 2 weeks and these goals will be reviewed every 4 weeks by the AHP.

DAMPAA also includes health education delivered from week 5 onwards during the physical activity session in a group yarning style. Sessions will be delivered by the AHP and exercise professional in a semi-structured yarning style method. Sessions include topics on safety and benefits of walking and yarning, diabetes prevention and management, falls prevention, good tucker (nutrition), well-being and connection and community service access. Medication reviews will be conducted by a pharmacist during the action period in a face-to-face meeting with each participant at the relevant study site. Each participant’s general practitioner (GP) will be sent a letter detailing the outcome of the review, which may include recommendations for medication changes. The study coordinator will contact GPs to determine if recommended changes were made. Participant attendance will be recorded to measure adherence to sessions, while an AHP and exercise professional will ask if the participant completed home session/s, as well as the RPE to measure intensity of the home session. Strategies to maintain adherence to the programme include providing transport; building group connection through yarning, group-themed shirts and encouraging a buddy system for home sessions; group walking outside in nature when possible, phone call reminders the day before each session and providing a culturally safe inclusive environment with Aboriginal and non-Aboriginal health professional research staff that have undergone cultural sensitivity training and are experienced working with Aboriginal people. At the conclusion of the action period, participants will complete a 6-month follow-up assessment consisting of visits 1 and 2 (figure 1). The maintenance period will consist of three walking and yarning sessions per week with all sessions completed by the participants at home or in community parks or other programmes. Participants will be provided with a file containing their weekly programme, instruction sheets and a monthly activity calendar. DAMPAA staff will monitor weekly progress through a telephone call or text message. Staff will ask participants how many walking and yarning sessions they completed that week, and the RPE for each session to measure the intensity. At the end of the maintenance period, participants will complete a 12-month assessment consisting of visit 1 and 2 and process evaluation interviews regarding their assessment and programme experiences.

### Usual care group

Participants randomised to the usual care group will be followed-up with 6 and 12-month assessments (repeat of visit 1 and visit 2 on each occasion). Participants are sent a general dementia education pamphlet via mail within 2 weeks of randomisation by the Aboriginal health practitioners. The pamphlet contains brief information on dementia risk factors for Aboriginal people.

#### Outcomes

The primary outcomes will be cognition (measured by the KICA-Cog), daily function (measured by the KICA-Function tool) and quality of life (measured by the Good Spirit, Good Life (GSGL)^34 35^ andEQ-5D-5L tools.^44^ Secondary outcomes are described in table 1. Outcome measures will be recorded at baseline, 6 months and 12 months. Death will be followed-up with next of kin.

**Table 1 T1:** Secondary outcomes of the Dementia Prevention and Risk Management Program for Aboriginal Australians study

Secondary outcomes	Measure
Process outcomes (assumptions, resources and activities)	Yarning circles, surveys, in-depth interviews with staff members and participants
Death	Follow-up with next of kin
Cardiovascular risk factors	Resting mean systolic blood pressure (mm Hg). Mean cholesterol level (mmol/L). Glycosylated haemoglobin. Body weight, body composition and BMI (kg/m^2^). Waist and hip girths (cm). Smoking status – KICA smoking questionnaire. Alcohol intake – KICA alcohol questionnaire. Functional capacity (2 minute walk test). Regular physical activity - Rapid Assessment of Physical Activity. Medications – current medications and adherence.
Falls	Number of falls in previous 6 months

BMIbody mass indexKICAKimberley Indigenous Cognitive Assessment

Process outcomes will include the successful incorporation of (1) all DAMPAA ToC resources (figure 2) into the programme, (2) meeting of DAMPAA ToC assumptions (table 2) and (3) appropriate completion of ToC activities.^38^ These three steps will be explored through in-depth interviews with project staff and through surveys and/or yarning groups with participants.

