#### Sample size

Based on unpublished analyses of a cohort study of ageing well,^7^ we expect KICA-Cog scores to decrease by a mean of 2 points in the usual care group, and by 1 point in the DAMPAA programme group, with a common SD of 3 points. A sample size of 286 people (143 in each group) would be required to provide 80% power to detect this difference, given a two-sided significance level of 5%. For the secondary outcome of daily function, we expect that 60% of the usual care group would have a decline in at least one activity of daily living during the study period, compared with only 44% of people in the DAMPAA programme arm. A sample size of 304 people would provide 80% power to detect such a difference at the 5% significance level. For the quality of life outcomes, based on previous research^35^ we expect mean GSGL and EQ-5D-5L scores to increase by 2 points and 1 point, respectively, in the DAMPAA group and to remain unchanged in the usual care group. Assuming a common SD of 3 points, a sample size of 74 and 286 people, respectively, is required to have 80% power to detect these differences at the 5% significance level. To account for potential attrition, we plan to recruit a total of 320 people (160 people per group).

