#### Data management and analysis

Data will be stored securely on a protected University of Western Australia (UWA) Institutional Research Data Store. Data will be de-identified to maintain confidentiality. All quantitative data will be entered and analysed using the Stata statistical package, while qualitative data will be managed with NVivo (Lumivero, Denver, Colorado). The study will employ an intention-to-treat analysis including all randomised participants. This means that participants will be analysed as per their randomisation, rather than the treatment they ultimately receive. We will use a generalised linear mixed model to compare changes in the KICA-Cog (cognition, primary outcome measure) over time between the two groups, with a significantly greater decrease in KICA-Cog scores expected in the usual care group at 12 months. The covariates in this model will be the baseline KICA-Cog score, time (6 or 12, entered as a categorical variable), group (DAMPAA programme or usual care) and an interaction between group and time. Participant and site will be treated as random effects. Similar models will be run for the other outcomes which are a mixture of variable types (proportions, counts, etc). We will handle missing data by performing complete case analyses. Results will be reported in accordance with the Consolidated Standards of Reporting Trials statement.^46^

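### The article names four primary scores in some places and KICA-Cog alone in another; its 5% error and 80% power hold for the primary claim only if KICA-Cog is the sole primary

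*Protocol article*

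**What the plan says.** Four parts of the Protocol article bear on which outcome is primary.

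- **Abstract, Methods.** The primary outcome entry lists the KICA-Cog score, the KICA-ADL score and "quality of life (Good Spirit, Good Life and EQ-5D-5L scores". That is three domains and four scores.
- **Outcomes.** "The primary outcomes will be cognition (measured by the KICA-Cog), daily function (measured by the KICA-Function tool) and quality of life", with quality of life again measured by GSGL and EQ-5D-5L. Table 1, which sets out the secondary outcomes, does not include daily function.
- **Sample size.** "For the secondary outcome of daily function, we expect that 60% of the usual care group would have a decline" in at least one activity, against 44% in the programme arm. Separate totals are given for 80% power: 286 for KICA-Cog, 304 for daily function, 74 for GSGL and 286 for EQ-5D-5L. Each is at a 5% level with no adjustment. Planned recruitment is 320.
- **Data management and analysis.** The model is used "to compare changes in the KICA-Cog (cognition, primary outcome measure) over time between the two groups", and the greater decline under usual care is expected at 12 months. For the rest, "Similar models will be run for the other outcomes which are a mixture of variable types".

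**The concern.** Daily function is primary in two places and secondary in a third. The two quality-of-life scores are primary in two places and fall among the other outcomes in the analysis section. Only KICA-Cog is primary throughout.

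The number of primary outcomes decides what the 5% and the 80% refer to. Four separate calculations, each at 5%, control the error of each test alone. They do not control the error of a claim that the trial met a primary outcome when there are four chances to meet one, and they do not give 80% power for a claim that needs all four. As written, a report could call any of the four scores primary after the results are known and cite a section in support. A published protocol should prevent that.

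**Working it through.** **Inputs from the Sample size section.** KICA-Cog: mean decline 2 v 1, difference 1, SD 3. Daily function: 60% v 44%. GSGL: difference 2, SD 3. EQ-5D-5L: difference 1, SD 3. Level 5%, power 80%, 160 per arm recruited.

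**Assumption.** The article gives no correlation between the four test statistics, so a range from 0 to 0.7 is shown.

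**Step 1. Reproduce the plan's sample sizes (two-sided 5%).**
- KICA-Cog and EQ-5D-5L, standardised difference 1/3: the normal formula 2 × 3² × (1.96 + 0.842)² / 1² = 141.3 gives 142 per arm. The t-test version gives 143 per arm, total 286, as stated.
- GSGL, standardised difference 2/3: the t-test version gives 37 per arm, total 74, as stated.
- Daily function, pooled proportion 0.52, no continuity correction: [1.96√(2 × 0.52 × 0.48) + 0.842√(0.60 × 0.40 + 0.44 × 0.56)]² / 0.16² = 151.9 gives 152 per arm, total 304, as stated.

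All four figures are correct at an unadjusted 5% each.

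**Step 2. KICA-Cog as sole primary.** One test at 5% has error 5%. Power is 80% at 143 per arm and 84% at 160. The stated design holds.

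**Step 3. Any one of four counts as success.**
- Independent tests: 1 − 0.95⁴ = 0.185.
- Strict upper bound: 4 × 0.05 = 0.20.
- Equal positive correlation, by simulation of four normal statistics: 17.4% at 0.3, 15.6% at 0.5, 13.0% at 0.7.
- These count false findings in either direction. False benefit alone is about half: 9.6% if independent, 6.5% at 0.7.
- Splitting 5% equally (1.25% each) would restore control, but KICA-Cog power falls to 62% at 143 per arm and 68% at 160.

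**Step 4. All four required.** At 160 per arm with no attrition, the single-test powers are 0.844 (KICA-Cog), 0.820 (daily function), 1.000 (GSGL) and 0.844 (EQ-5D-5L).
- Independent: 0.844 × 0.820 × 1.000 × 0.844 = 0.58.
- Simulating four equally correlated normal statistics with these same single-test powers gives about 63% at 0.3, 67% at 0.5 and 71% at 0.7, all below 80%.

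**Step 5. Cost of a fixed order** (KICA-Cog, daily function, GSGL, EQ-5D-5L; 160 per arm, independent).
- Second: 0.844 × 0.820 = 0.69.
- Third: 0.69 × 1.000 = 0.69, against nearly 1.00 for GSGL tested alone.
- Fourth: 0.69 × 0.844 = 0.58.

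**The case against.** The analysis section largely settles the matter. It names one primary outcome measure and a time point, and the Sample size section's label for daily function points the same way. On that reading the primary claim carries no inflation. The 5% levels are sample-size inputs, and the analysis section sets no test level. A multiplicity or success rule may sit in an analysis plan that is not shown, so its absence from an article is no fault by itself.

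All of this stands, and it limits the point: the error rates in Step 3 are conditional on an any-of-four reading that no section states. It does not remove the contradiction. The Abstract and Outcomes sections are current text and say something different, and an unseen analysis plan could choose between the labels without making the article consistent.

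Two stronger readings are tempting.

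- A reader might infer that the group-by-time coefficient is the planned test. With baseline as a covariate and time coded 6 or 12, that coefficient is the 12-month effect minus the 6-month effect. But the article only lists it as a model term, never calls it the test, and places the expected difference at 12 months. The planned model can supply that contrast.
- A reader might count both visits and speak of eight chances of a false finding. The article points to 12 months for KICA-Cog, and two visits by the same people are not independent tests.

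**Conclusion.** The designation of primary outcomes contradicts itself and should be settled before analysis. The sample-size arithmetic is right, but it delivers 5% error and 80% power for the primary claim only under the single-primary reading. The any-of-four error of about 13% to 18.5% rests on assumed correlations from 0.7 to 0. The all-four joint power of about 58% rests on independence, full retention of 320 and the plan's own effect sizes. Neither is a property of a rule that the article has adopted. They show what is at stake while the labels leave the choice open.

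**What to change.** Issue an amendment dated before outcome data are unblinded or analysed.

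1. Make the between-group difference in KICA-Cog at 12 months, to which the analysis section already points, the single primary test at two-sided 5%.
2. Relabel daily function, GSGL and EQ-5D-5L as secondary outcomes, with a stated multiplicity rule such as Holm or a fixed order.
3. Use the same labels in the Abstract, Outcomes (including Table 1), Sample size, and Data management and analysis.

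**Cost.** No new participants are needed, because 286 already sizes KICA-Cog alone at 5%. Larger numbers are not an option anyway, since the article says the last enrolment was in October 2023. The change is more than editorial: three listed primary scores lose that status, late in the trial. If they are gated behind KICA-Cog their power falls, to about 69% for GSGL in third place and about 58% for the last of four, under independence. Which multiplicity rule to use is the investigators' choice, provided that it is written down in advance.
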